**Title:**

**Effects of intra-operative Pressure Support Ventilation during general anesthesia: A randomized Controlled Study**

**1. Objective:** Evaluate the safety and efficiency of Pressure Support Ventilation (PSV) mode during general anesthesia in orthopaedic surgery.

**2. Hypothesis of the work:** Pressure Support Ventilation (PSV) allows a reduction of emergence time to extubation, anaesthetic drugs consumption, and improves main ventilatory parameters in comparison to the 2 main standards of care as spontaneous breathing (SB) and controlled mechanical ventilation (CMV).

**3. Primary end point:** The primary end point is LMA removal time with PSV in comparison to CMV. The removal time (open mouth to command) of the LMA will be determined by questioning every minute the patient. The emergence time will be defined as the time to obtain a 10 point score on a five questions test. Each of the following items:1) month of birth; 2) date of surgery; 3) day of the week; 4) address of the patient; 5) simple addition, will scored 0 (no response), 1 (inexplicit response) or 2 (good response).

**4. Secondary end points:**

**-** Total drugs consumption used during TIVA recorded at the end of the surgical procedure.

- Total drugs consumption during TIVA (except induction dose) normalized to weight and duration of TIVA expressed in mg kg-1 min-1 for propofol and µg kg-1 min-1 for fentanyl.

- Hemodynamic (Heart rate, MAP) and ventilatory variables (RR, VTi, VTe, Ti/Ttot, maximal and plateau pressures, SpO2, PetCO2) recorded during a 2-min stable state for each period.

- Peak pressure, plateau pressure and flow will be measured with Capnomac Ultima at the tube opening.

- Airway leaks will be determined by noting the difference between inspired and expired tidal volume (VTi-VTe).

- Airway occlusion pressure (P0.1) will be measured at each point except in T1, T2 and T3 for the CMV group. For T0 and T4, ventilatory variables will be obtained in awake patients spontaneously breathing through the circuit via a mouth piece with a nose clip.

- Presence or absence of methylene blue regurgitation at the end of surgery will be evaluated by an airway fiberoscopy throughout the LMA.

**5. Ethic considerations :** CCPPRB (Comité consultatif de protection des personnes dans la recherche biomédicale) University Hospital of Montpellier, Ethics committee – Montpellier Méditerranée. France 34000.

Informed written consent will be obtained from all patients.

**6. Study design:** prospective randomized control trial including three parallel groups.

All data will be recorded at baseline (T0: before TIVA induction), 10 min after TIVA induction (T1), at the surgical incision (T2), at the end of anaesthetic drugs infusion (T3) and when the patient will be totally awake (T4).

Figure 1 summarizes the study design.

**7. Inclusion criteria:** ASA physical status I and II patients scheduled for elective knee arthroscopic surgery under total intravenous anesthesia (TIVA) with a classic laryngeal mask airway (LMA) and mechanical ventilation.

**8. Exclusion criteria:** emergency procedures**,** ASA physical status > II, refusal patient.

**9. Randomization procedure:** in operating room (OR), the patients will be allocated randomly into three groups (SB, CMV and PSV). The investigators will generated a random-number table on a computer, used the table to prepare envelopes for random patient allocation.

**10. Premedication protocol anesthesia:** oral hydroxyzine (1 mg kg-1) and a gelule of methylen blue (2 mg).

**11. Protocol general anesthesia:** TIVA will induced using propofol 2.5 mg kg-1, fentanyl 2 µg kg-1 and will be maintained with propofol 0.05 mg kg.-1 min-1 and fentanyl 0.02 µg kg-1 min-1 with nitrous oxide in oxygen, with a fraction of inspired oxygen of 0.4.

The anaesthetic regimen will be individually adapted to hemodynamics variables according the standard of care of our center. Briefly, additional boluses of propofol 0.25 mg/kg and fentanyl 25 µg will be given in case of a 20 beat min-1 increase in heart rate and/or a 25% increase in MAP during 2 min.

**12. Airway management** = LMA (size 4, females; size 5, males) will be inserted according to the manufacturer’s instructions (Laryngeal MaskCo., Henley-on-Thames, UK). The volume of air in the cuff will adjusted at an airway sealing pressure greater than 15 cmH2O.

**13. Ventilator and delivered mechanical ventilation** = Mechanical ventilation will be delivered by a Servo 900C ventilator Siemens-Elema, Solna, Sweden which is the only available ventilator with PSV mode in the operating room during the study period. In SB-group, patients will breath spontaneously throughout the ventilator circuit, in CMV-group, patients will be ventilated in CMV (expiratory tidal volume: VTe of 8 mL/kg, a respiratory rate (RR) of 10 cycles/min and an inspiratory/total duty cycle (Ti/Ttot) ratio of 1:3 with a time plateau pressure at 15% of the inspiratory time) and in PSV-group patients will receive PSV (PSV level will be set to obtain a VTe between 7-8 mL/kg and RR between 10-16 cycles/min, inspiratory trigger will be fixed at -2 cmH2O and the termination of inspiratory support will be fixed at the drop of flow at 25% peak inspiratory flow value). Ventilation will be performed with zero positive end expiratory pressure in all three groups.

**14. Respiratory and hemodynamic monitoring:** Monitoring will including electrocardiography (ECG), mean arterial blood pressure (MAP) (monitored noninvasively), pulsoxymetry (SpO2) and end expiratory concentrations of oxygen, carbon dioxide (PetCO2), and nitrous oxide (Capnomac Ultima; Datex-Ohmeda, Helsinki, Finland). The Capnomac Ultima (Datex-Ohmeda, Helsinki, Finland) will be used to continuously monitor the airway pressures and flow waveforms which allowed detection of the wasted inspiratory effort on the expiratory part of the flow waveform.

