**15. Statistical analysis:**

The primary end point is LMA removal time with PSV in comparison to CMV.

The secondary end points are respiratory variables and total anaesthetic drugs consumption. Previous studies have shown that TIVA emergence time with LMA removal in CMV patients ranges from 15-20 min, with an average of 18 min and an SD of 6 min. We postulate a difference of 50% in the LMA removal time in the PSV group. Therefore, accepting a type I error risk of 5% and a type II error risk of 20% (power 80%), 12 patients would be required in each group to evaluate our hypothesis. Data will be expressed as mean ± SD. Comparison of two means will be performed using the Student t test. Comparison of several means will be performed using repeated-measures analysis of variance and the Newman-Keuls test. *P<*0.05 will considered as significant.

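### At T1-T3, respiratory rate and expired tidal volume are set in CMV and titrated in PSV, so testing them as end points against CMV tests the ventilator settings, not the mode

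*Protocol*

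**What the plan says.** Section 2 (Hypothesis) states that PSV "improves main ventilatory parameters in comparison to the 2 main standards of care as spontaneous breathing (SB) and controlled mechanical ventilation (CMV"). It does not say which parameters are the main ones, or what value would count as better.

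Section 4 (Secondary end points) lists "ventilatory variables (RR, VTi, VTe, Ti/Ttot, maximal and plateau pressures, SpO2, PetCO2) recorded during a 2-min stable state for each period". It adds leak, defined as VTi minus VTe, and P0.1. On P0.1 it says: "Airway occlusion pressure (P0.1) will be measured at each point except in T1, T2 and T3 for the CMV group". At T0 and T4 all patients are awake and breathing spontaneously through a mouthpiece.

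Section 15 (Statistical analysis) confirms the status of these variables: "The secondary end points are respiratory variables and total anaesthetic drugs consumption". Two means are compared by Student's t test, and several means by repeated-measures ANOVA with Newman-Keuls. The threshold is P<0.05.

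Section 13 (Ventilator) fixes the ventilation. For CMV it sets "expiratory tidal volume: VTe of 8 mL/kg, a respiratory rate (RR) of 10 cycles/min", with Ti/Ttot 1:3 and a plateau lasting 15% of inspiratory time. For PSV, "PSV level will be set to obtain a VTe between 7-8 mL/kg and RR between 10-16 cycles/min", and inspiration ends when flow falls to 25% of its peak. SB patients breathe unaided through the circuit.

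**The concern.** An end point can show a treatment effect only if the treatment is free to move it. At T1, T2 and T3 the protocol decides RR and VTe in CMV outright and confines them to a band in PSV. It also decides Ti/Ttot in CMV. The same three variables are then secondary end points, tested at P<0.05, under a hypothesis that PSV improves ventilation compared with CMV.

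A significant PSV-CMV difference in RR or VTe would therefore show that the operators followed section 13. Because improvement is not defined, a higher rate or a smaller tidal volume could be read as support for the hypothesis or as evidence against it. Either way, the settings would decide one of the three parts of the stated hypothesis (the other two being emergence time and drug consumption).

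**Working it through.** **Step 1. Which listed variables are set at T1-T3 (sections 4 and 13)**

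| Variable | CMV | PSV | SB |
|---|---|---|---|
| RR | set, 10/min | titrated, 10-16/min | free |
| VTe | set, 8 mL/kg | titrated, 7-8 mL/kg | free |
| Ti/Ttot | set, 1:3 | free (flow-cycled) | free |
| VTi, leak (VTi-VTe), SpO2 | not set | not set | free |
| Peak pressure | not set directly | depends on the PSV level chosen | free |
| Plateau pressure | plateau described | none described | none described |
| P0.1 | not measured | measured | measured |

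**Step 2. Direction of the PSV-CMV contrast if section 13 is followed**

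- RR: every PSV value is at least 10 and every CMV value is 10, so mean(PSV) - mean(CMV) lies between 0 and 16 - 10 = +6/min.
- VTe: every PSV value is at most 8 and every CMV value is 8, so mean(PSV) - mean(CMV) lies between 7 - 8 = -1 and 0 mL/kg.
- Ti/Ttot: a patient-driven value in PSV is compared with a constant in CMV.

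The sign of the first two differences is settled before any patient is enrolled.

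**Step 3. Knock-on for PetCO2**

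Minute ventilation = VTe x RR.

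- CMV: 8 x 10 = 80 mL/kg/min.
- PSV: from 7 x 10 = 70 to 8 x 16 = 128 mL/kg/min.
- Ratio to CMV: 70/80 = 0.875 to 128/80 = 1.6.

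PetCO2 is not set directly, but part of any PSV-CMV difference in it follows from these targets.

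**Step 4. How often would the tests be significant?**

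The protocol gives neither the spread of PSV values within the band nor the delivery noise, so both are assumptions here. Each figure is the share of 5,000 simulated trials with P<0.05 (t test, 12 per group, PSV uniform over the stated range).

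Noise in CMV only:

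| Variable and PSV range | CMV SD | Significant |
|---|---|---|
| RR 10-16 | 0.01 to 0.5/min | 100% |
| RR 10-12 | up to 0.5/min | at least 99% |
| VTe 7-8 | 0.1 / 0.3 / 0.5 mL/kg | 100% / 98% / about 82% |
| VTe 7.5-8 | 0.1 / 0.3 / 0.5 mL/kg | above 99% / about 70% / about 37% |

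The same noise added to both groups:

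| Variable and PSV range | SD | Significant |
|---|---|---|
| RR 10-16 | 1/min | near 100% |
| RR 10-12 | 1/min | about 57% |
| VTe 7-8 | 0.3 / 0.5 / 1.0 mL/kg | about 90% / 58% / 22% |

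The rate varies widely with the assumptions. In every row the underlying difference is produced only by the prescribed targets.

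**Step 5. P0.1**

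Of the five time points, T1, T2 and T3 are the intra-operative ones, and section 4 excludes CMV at all three. There are no intra-operative CMV values with which to compare PSV.

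**The case against.** The best defence is that the hypothesis does not name RR, VTe or Ti/Ttot as its criteria, that much of the list is not set by the protocol, and that the damage is limited. Most of this stands. SpO2, VTi and leak are not prescribed; VTi in particular carries the leak once VTe is targeted. In SB nothing is set, so PSV versus SB on P0.1, SpO2 or PetCO2 is a real comparison of modes. The defence does not remove the core: section 4 lists the set variables as end points without distinction, and section 15 tests respiratory variables at P<0.05.

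A reader might infer more than the protocol supports:

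- *That the P0.1 analysis cannot be run.* Nothing in the protocol specifies a three-group P0.1 model. Its own exclusion leaves PSV and SB during surgery, and the stated tests can compare those two.
- *That plateau pressure exists only in CMV and should be dropped elsewhere.* Section 13 describes a plateau for CMV and is silent on the others, while section 4 plans the measurement without excluding any group. Silence is reason for caution, not for deletion.
- *That a significant result is certain.* Values are recorded over two minutes through a mask that can leak, so they need not equal the targets. Step 4 shows that the rate can fall well below 100%.
- *That near-zero variance in CMV invalidates the test.* With 12 per group, equal means and SDs of 1 and 0.01, the simulated type I error of the t test was 6.1%, a small excess over 5%. The three-group ANOVA was not examined.

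**Conclusion.** The point holds for secondary end points at T1-T3. Provided section 13 is followed, the PSV-CMV contrasts on RR and VTe have a direction fixed by design (0 to +6/min and -1 to 0 mL/kg), and the Ti/Ttot contrast sets a free value against a constant. None of the three can show an effect of the mode relative to CMV. PetCO2 is affected in part, through a permitted minute ventilation of 0.875 to 1.6 times that in CMV. The direction of the RR and VTe contrasts rests only on the protocol's own settings; the rejection rates rest on assumed spread and noise, and are illustrative.

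RR and VTe are also poor evidence of improvement in PSV versus SB, because PSV is titrated on both. Intra-operative P0.1 can inform PSV versus SB but cannot support a claim against CMV.

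The protocol does not support reading this as a flaw in the whole trial. The primary end point (LMA removal time) is untouched. So are the T0 and T4 comparisons, when every patient breathes spontaneously. The consequence is confined to the ventilatory part of the hypothesis.

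**What to change.** Change sections 2, 4 and 15 in wording and analysis only; the ventilator settings are not in question.

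- At T1-T3, report RR, VTe and Ti/Ttot by group as delivered ventilation, with no significance test against CMV. Do not count RR or VTe as evidence of improvement over SB either.
- Name the variables and group pairs on which ventilatory improvement is judged, using those not directly set: SpO2, leak (VTi-VTe), and PetCO2 shown beside delivered minute ventilation. Read peak pressure alongside the PSV level used.
- State that intra-operative P0.1 is a PSV versus SB comparison.
- Keep plateau pressure as a measured variable, but base no PSV-CMV claim on it unless a comparable plateau is obtained in both groups.

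The cost is fewer formal tests against CMV, and those given up are uninformative about the mode. No new data are needed.

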**15. Statistical analysis:**

The primary end point is LMA removal time with PSV in comparison to CMV.

The secondary end points are respiratory variables and total anaesthetic drugs consumption. Previous studies have shown that TIVA emergence time with LMA removal in CMV patients ranges from 15-20 min, with an average of 18 min and an SD of 6 min. We postulate a difference of 50% in the LMA removal time in the PSV group. Therefore, accepting a type I error risk of 5% and a type II error risk of 20% (power 80%), 12 patients would be required in each group to evaluate our hypothesis. Data will be expressed as mean ± SD. Comparison of two means will be performed using the Student t test. Comparison of several means will be performed using repeated-measures analysis of variance and the Newman-Keuls test. *P<*0.05 will considered as significant.

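### The 12 patients per group in Section 15 do not follow from the inputs given; those inputs need 9, so the sample is larger than required and the stated power is understated

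*Protocol*

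**What the plan says.** Section 15 of the Protocol names one powered comparison: "The primary end point is LMA removal time with PSV in comparison to CMV". For control patients it reports a range from earlier work, "TIVA emergence time with LMA removal in CMV patients ranges from 15-20 min", and then the planning values, "with an average of 18 min and an SD of 6 min". The target effect is given as "We postulate a difference of 50% in the LMA removal time in the PSV group". The type I error follows, "accepting a type I error risk of 5"%, and the sentence then gives the type II error and, as a deduction from all of this, the number of patients: "type II error risk of 20% (power 80%), 12 patients would be required in each group". Two means are to be compared by the Student t test. Section 6 describes three parallel groups, so the total is 3 × 12 = 36. The sample-size text mentions no dropout allowance, no multiplicity adjustment and no SD other than 6 min, and it does not say whether the 5% is one- or two-sided.

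**The concern.** Every input that a two-group sample-size calculation needs is printed, apart from the sidedness of the test, and the number of patients is presented as their consequence. A reader can therefore repeat the calculation, and it gives a clearly smaller number. The effect, SD, power and sample size do not fit together as written.

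What is at stake is traceability. This is the only sample-size justification in the Protocol. Anyone judging the 36 patients, or later reading the PSV-CMV result, cannot tell which effect the trial was built to detect, or whether an unstated allowance lies behind the number.

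**Working it through.** **Inputs, all from Section 15 of the Protocol**
- Control mean 18 min, SD 6 min (SD taken as equal in both groups).
- Difference 50%: 0.50 × 18 = 9 min, i.e. PSV mean 9 min.
- Type I error 5% (two-sided assumed, one-sided also tried); power 80%.
- Student t test, equal groups.
- Stated result: 12 per group.

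**Step 1. Standardised difference.** d = 9 / 6 = 1.5.

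**Step 2. Attempt to reproduce 12, normal approximation.** n per group = 2 (1.96 + 0.8416)² / d² = 2 × 7.849 / 2.25 = 6.98, so 7.

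**Step 3. Same calculation for the t test.** Power comes from the noncentral t distribution with 2(n − 1) degrees of freedom and noncentrality d√(n/2).

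| n per group | Power for 9 min |
|---|---|
| 8 | 79.7% |
| 9 | 84.8% |
| 10 | 88.7% |
| 11 | 91.7% |
| 12 | 93.9% |

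The exact solution for 80% is n = 8.06, so 9 per group. The stated 12 is not reproduced. It exceeds 9 by 3 per group (33%), or 36 against 27 over three groups.

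**Step 4. What 12 per group delivers at 80% power.** The detectable d is 1.197. With SD 6 that is 1.197 × 6 = 7.18 min, or 7.18 / 18 = 39.9% of the control mean. Alternatively, holding the difference at 9 min, it corresponds to an SD of 9 / 1.197 = 7.52 min.

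**Step 5. Could another reading give 12?** t test, two-sided 5% and 80% power unless noted.

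| Variant | n per group | Stated in Section 15? |
|---|---|---|
| One-sided 5% | 7 | No |
| 90% power | 11 | No, 80% is stated |
| 95% power | 13 (12 by normal approximation) | No, 80% is stated |
| Bonferroni for three pairwise comparisons | 11 (85% power at 12) | No |
| Three-group ANOVA, SB mean assumed 13.5 min | 10 (89% power at 36 in total) | No |
| Rank-test efficiency 0.955 / 0.864 | 9 / 10 | No |
| Log scale | 5 | No |
| Control mean 15 min, difference 7.5 min (d = 1.25) | 12 (79.6% at 11, 83.3% at 12) | 15 is printed as the low end of the range, not as the planning mean |
| 9 per group plus 25% attrition: 9 / 0.75 | 12 | No |
| 9 per group plus 20% attrition: 9 / 0.80 = 11.25 | 12 | No |
| 50% read as CMV half as long again as PSV (18 v 12 min, d = 1.0) | 17 (65% power at 12) | Not the natural reading |

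Every route to 12 replaces a stated input or adds an unstated one.

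**The case against.** The strongest reply is that nothing is harmed. The trial meets its 80% target with room to spare, and the randomisation, endpoint and test are untouched. That stands, and it is why the point is minor.

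Next, 12 is not arbitrary. A planner who cautiously took 15 min, a figure printed in the same sentence, would obtain exactly 12. One who added about 25% for attrition to 9 would also obtain 12. This stands as a plausible explanation, but it does not cure the text: 18 min is given as the average, no attrition is mentioned, and 12 is said to follow from the values listed.

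It can also be said that 80% is a planning target and not a claim that 12 patients deliver exactly 80%. That is fair, but the sentence says 12 are required to meet the target, and on its inputs 9 suffice.

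Two stronger inferences should be resisted. A reader told that the stated power is wrong might take the primary comparison to be underpowered; the arithmetic shows the opposite. The 65% figure arises only if the 50% is measured against the PSV time, whereas the text gives the control mean and then a 50% difference in the PSV group. A reader might also conclude that one of the printed inputs must be misreported. That is not established: an undocumented attrition allowance would leave all of them correct.

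**Conclusion.** The deduction in Section 15 is wrong as written. A two-sided 5% Student t test with a 9 min difference and SD 6 min needs 9 per group for 80% power, against 12 stated; at 12 the power is about 94%. The error is in the safe direction and makes the sample 3 per group larger than its justification supports. The Protocol does not show where the extra patients come from. The result rests on two assumptions: a two-sided test, and the same SD of 6 min in both groups. A one-sided test widens the gap (7 per group, 97% power at 12). Severity: minor.

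**What to change.** Keep 12 per group and keep the 50% target. Correct the sentence in Section 15 in one of two ways:

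- If 12 was simply chosen, state what it delivers: with 12 per group, SD 6 min and a two-sided 5% test, power is about 94% for a 9 min (50%) difference and 80% for about 7.2 min. The 7.2 min figure describes the sample; it should not replace the sponsor's 50% as the target effect.
- If 12 came from a cautious control mean, a larger SD or a dropout allowance, state that figure and derive 12 from it.

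The cost is one sentence. No patients are added and the design does not change.

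### Newman-Keuls, named in section 15 for comparing several means, does not control family-wise error beyond three means; across 15 group-by-time means, false group differences in a secondary variable can reach 15–23%

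*Protocol*

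**What the plan says.** Section 15 of the Protocol assigns a Student t test to comparisons of two means. For more than two it says: "Comparison of several means will be performed using repeated-measures analysis of variance and the Newman-Keuls test". The threshold for P is given once, for all tests ("0.05 will considered as significant"). The section does not say which means form the Newman-Keuls family (three group means, five time means or all cells), nor whether a significant ANOVA must come first.

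Section 6 describes a "prospective randomized control trial including three parallel groups" and sets the measurement times: "All data will be recorded at baseline (T0: before TIVA induction), 10 min after TIVA induction (T1), at the surgical incision (T2"), followed by T3 at the end of drug infusion and T4 when fully awake. That is 3 × 5 = 15 means per variable. Section 4 lists ten haemodynamic and ventilatory variables, plus leak and P0.1. P0.1 is not measured in the CMV group at T1–T3, which leaves 15 − 3 = 12 means.

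The primary end point, in sections 3 and 15, is LMA removal time, PSV against CMV.

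**The concern.** Newman-Keuls ranks the means and tests ranges downwards, with a critical value that shrinks as the range spans fewer means. If all means are equal, the error is 5%. If real differences split the means into clusters, each cluster of truly equal means is tested at its own 5% and the errors add up. This design produces such clusters: a variable may change over time whatever the group, while the groups are equal at some or all time points.

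The section 2 hypothesis includes better ventilatory values with PSV than with both other modes, and section 15 makes the respiratory variables secondary end points. Claims of that kind would rest on these follow-up comparisons. A multiple-comparison test is there to limit false positives, and beyond three means this one does not do so reliably.

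**Working it through.** **The plan's own figures.** The 5% threshold is a bare rule with nothing to reproduce. The only calculated figure is the sample size of 12 per group ("accepting a type I error risk of 5% and a type II error risk of 20% (power 80%), 12 patients would be required in each"). It comes from a CMV mean and SD ("with an average of 18 min and an SD of 6 min") and a 50% difference, that is 9 min. The normal formula gives 2 × (1.96 + 0.84)² × (6/9)² ≈ 7 per group. The exact t test gives 79.7% power at 8, 84.8% at 9 and 94% at 12. Twelve is therefore not reproduced, but it exceeds what the stated inputs need. It does not bear on this point, except that 12 is used below as the group size.

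**Worst case for Newman-Keuls.** With k means, the most harmful pattern is well-separated pairs of equal means, which gives 1 − 0.95^m with m = k/2 rounded down.

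- k = 3: 1 − 0.95 = 5.0% (simulated: 4.7% with all equal, 5.0% with one mean far away)
- k = 5: 1 − 0.95² = 9.75% (simulated 9.7%)
- k = 12: 1 − 0.95⁶ = 26.5%
- k = 15: 1 − 0.95⁷ = 30.2%

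**Group differences at the same time point.** These are what the hypothesis is about. If the five time levels lie far apart and the three groups are equal at each, there are five clusters of three means: 1 − 0.95⁵ = 22.6% with independent errors.

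The full step-down on 15 cells was simulated with 12 patients per group, pooled within-cell variance as error, and 4,000 runs per entry. The correlation between time points within a patient is an assumption (0 to 0.7), because the Protocol gives none. Each entry is the percentage of variables with at least one false same-time group difference. In brackets is the rate when a significant group or interaction F is required first.

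| True pattern | 0 | 0.3 | 0.5 | 0.7 |
|---|---|---|---|---|
| All 15 means equal | 1.7 (1.3) | 1.2 (1.0) | 1.3 (1.2) | 1.1 (1.1) |
| Five separate time levels, no group difference | 22.7 (7.2) | 19.8 (7.0) | 18.3 (6.7) | 14.9 (5.8) |
| Five separate time levels, SB differs at T1–T3 | 22.1 (22.1) | 21.4 (21.4) | 18.0 (18.0) | 16.9 (16.9) |
| Awake and anaesthetised levels only, no group difference | 4.0 (2.2) | 3.8 (2.4) | 3.5 (2.7) | 3.1 (2.7) |
| Awake and anaesthetised levels only, SB differs at T1–T3 | 4.4 (4.4) | 4.5 (4.5) | 3.9 (3.9) | 3.2 (3.2) |

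The time levels in the table are 10 SD apart, but the result does not need such a gap: at zero correlation, steps of 1 SD already gave 19.9%. A separate simulation of the two-level pattern without group differences gave 4.8% (4.5% at correlation 0.5), so about 3–5% is a fair statement for that case. Counting false time differences as well, the two-level pattern gives 1 − 0.95² = 9.75% (simulated 9.7%).

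**Comparison.** With five separate levels, Tukey over all 15 cells gave about 1%. Tukey run separately at 5% at each of five time points gave 22–23% under independence, because the repetition and not the test drives that figure.

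**The case against.** A reader might infer that the plan will produce false group differences in about 20% of variables. The documents do not support that. The figure needs all cells in one family, five distinct time levels and a low to moderate correlation; the Protocol states none of these. If only awake and anaesthetised states differ, the rate is about 3–5%. If the three group means alone are compared, Newman-Keuls holds 5%. If the three groups are compared afresh at each time point, up to 22.6% arises with any test used at 5% each time.

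A reader might also infer that the plan breaks a 5% family-wise error it has promised. It has not: the type I error of 5% in section 15 belongs to the sample size for the primary end point, and no family-wise level is promised for secondary variables.

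An ANOVA gate would help when no group differs. It fails once one group truly differs, and section 13 makes that plausible: SB patients breathe unaided, CMV has a set tidal volume and rate, and PSV is adjusted to a target range. For those set or targeted variables, equality of all groups at T1–T3 is not a representative null. True nulls can still sit beside real differences, for example at T0, before the modes are applied.

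The exact family could be left to an analysis plan that is not shown. The test is not left open, however: section 15 names it. These limits make the rate conditional and put family and test on an equal footing. They do not make Newman-Keuls suitable for 5 to 15 means.

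**Conclusion.** The concern holds in a conditional form. Section 15 fixes a procedure that lacks family-wise control beyond three means, in a design with up to 15 means per variable. With all cells in one family and no gate, the false same-time group-difference rate per variable depends on how the time levels are spaced: about 3–5% for two levels and about 15–23% for five, with the correlation between 0.7 and 0 as an assumption. A significant ANOVA as a precondition brings the upper range down to about 6–7% only when no group differs.

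The consequence is confined to secondary haemodynamic and ventilatory variables. The primary comparison is of two means by t test and stands as planned. The change should be made, but it does not threaten the trial's main conclusion.

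**What to change.** Replace Newman-Keuls in section 15 and state, for each variable, the family over which error is controlled. Two options:

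- **Holm over pre-stated contrasts.** PSV–CMV and PSV–SB at T1, T2 and T3 taken together: 2 × 3 = 6 contrasts, the smallest P being compared with 0.05/6 = 0.0083. For P0.1 only PSV–SB is possible, so 3 contrasts, starting at 0.05/3 = 0.0167.
- **Tukey over all cells of the variable,** if every pairwise comparison is wanted. It should not be run separately at 5% at each time point, which would bring the inflation back.

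The cost is a sentence or two in section 15. Critical values are somewhat larger than Newman-Keuls uses for neighbouring means, so power for secondary comparisons falls slightly. Sample size and the primary analysis do not change.

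### For RR, Ti/Ttot and VTe per kg at T1-T3, the common error term of the planned repeated-measures ANOVA is invalid by design, so the PSV-SB standard error is wrong, in a direction the protocol does not settle

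*Protocol*

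**What the plan says.** Protocol, Section 15 compares several means by "repeated-measures analysis of variance and the Newman-Keuls test". It adds nothing on the error term, unequal variances or correlation over time.

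Protocol, Section 4 makes the following secondary end points: "ventilatory variables (RR, VTi, VTe, Ti/Ttot, maximal and plateau pressures, SpO2, PetCO2) recorded during a 2-min stable state for each period". Section 6 sets five recording times: T0 before induction, T1 to T3 between induction and the end of drug infusion, and T4 when fully awake. At the first and last, Section 4 has every patient breathing unaided: "For T0 and T4, ventilatory variables will be obtained in awake patients spontaneously breathing through the circuit".

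Protocol, Section 13 defines the arms:
- CMV: "VTe of 8 mL/kg, a respiratory rate (RR) of 10 cycles/min and an inspiratory/total duty cycle (Ti/Ttot) ratio of 1:3".
- PSV: "PSV level will be set to obtain a VTe between 7-8 mL/kg and RR between 10-16 cycles/min".
- SB: "In SB-group, patients will breath spontaneously throughout the ventilator circuit", with no setting or target.

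**The concern.** Repeated-measures ANOVA and the Newman-Keuls test, as usually run, estimate one error variance and apply it to every pairwise comparison. That is sound only if the groups share a variance. Here the interventions themselves set the spread of some outcomes. At T1-T3, RR and Ti/Ttot in CMV are machine settings and should hardly vary between patients; VTe per kg is also set. PSV is held to a range and SB is free. The inequality can be foreseen before any data are collected.

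PSV against SB is the comparison that suffers. CMV contributes to its error term but says nothing about how variable PSV or SB patients are. The comparison matters because the hypothesis in Section 2 claims better ventilatory parameters with PSV than with either standard, SB included. Equal group sizes do not protect a pairwise contrast from this problem.

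**Working it through.** **Inputs.** 12 per group and a 5% type I error come from Section 15 (tests taken as two-sided). The 12 was derived for LMA removal time; it serves here only as n. The protocol states no figure for the ventilatory variables, so there is none to reproduce. It gives no SDs or within-patient correlations either. These are assumed: SB SD 1 (the unit), PSV SD 0.2 to 1, CMV SD at T1-T3 0 or 0.5, awake SD 0.5 to 2 in all groups.

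**1. Error pooled over three groups at one of T1-T3.** The pooled standard error relative to the contrast's own is

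√[(s²PSV + s²SB + s²CMV)/3] ÷ √[(s²PSV + s²SB)/2].

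- PSV 1, SB 1, CMV 0: √(2/3) ÷ 1 = 0.816, that is 18% too small.
- PSV 1, SB 1, CMV 0.5: √(2.25/3) = 0.866, 13% too small.

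With CMV SD 0 and equal PSV and SB SDs the false-positive rate is exact. The pooled test uses 33 degrees of freedom (critical t 2.03) but rejects whenever the ordinary two-group t on 22 degrees of freedom exceeds 2.03 × 0.816 = 1.66. That happens in 11.1% of trials. Simulation agrees (11.1%) and gives about 9% for CMV SD 0.5. A Welch test stays at about 5%.

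**2. The Newman-Keuls critical value.** The 11% applies when PSV and SB are adjacent means, so that the two-mean critical value is used. If they are the two extremes of the three, the critical value is 3.47/√2 = 2.45. Then 2.45 × 0.816 = 2.00 on 22 degrees of freedom gives about 5.8%, against about 2% with equal variances. If the CMV mean lies well apart (5 SD, assumed), the full step-down procedure gives 10.9% with CMV SD 0 and 8.9% with CMV SD 0.5, against 5.1% with equal variances.

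**3. Error pooled over all 15 group-by-time cells.** Six cells are awake (three groups at T0 and T4) and nine anaesthetised. With PSV = SB = 1, CMV = 0 at T1-T3 and awake SD a, the mean cell variance is (6 × 1 + 3 × 0 + 6a²)/15. The ratio is its square root.

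| Awake SD a | Ratio | False positives (simulated) |
|---|---|---|
| 0.5 | √0.5 = 0.71 | about 17% |
| 1 | √0.8 = 0.89 | about 8% |
| 1.5 | √1.3 = 1.14 | about 2.7% |
| 2 | √2 = 1.41 | about 0.7% |

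The direction turns where 6 + 6a² = 15, at a = √1.5 = 1.22.

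It also depends on how tightly PSV is held. With PSV SD 0.5 and a = 1, the mean cell variance is (3 + 0.75 + 6)/15 = 0.65 against 0.625 for the contrast: ratio √(0.65/0.625) = 1.02, false positives about 5%. With PSV SD 0.2 and a = 1 it is 9.12/15 = 0.608 against 0.52: ratio 1.08, false positives about 3.5%.

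**The case against.** **The direction is not established.** A reader might infer that the PSV-SB standard errors are simply too small and that false positives double. The documents do not support that. Section 6 records everything at T0-T4, and at T0 and T4 all groups breathe freely. Once those times enter the error term, the error can run either way, depending on an awake SD the protocol does not give. The 11% belongs to one form of the analysis and to the two-mean critical value. This objection stands.

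**Few variables are affected.** RR and Ti/Ttot are the clear cases. VTe is set per kg; in mL it varies with body weight, and Section 4 itself expects leak between inspired and expired volume. Pressures, SpO2, PetCO2, heart rate and MAP are not among the values the CMV settings fix. This stands too.

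**Non-sphericity cannot be sized.** Awake and anaesthetised times make equal correlations implausible, but any figure would rest on an invented correlation matrix. None is claimed.

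**It may be detail for the SAP.** Section 15 does not say that the error is pooled; that is the usual form of the named tests, and a SAP not shown may specify otherwise. This limits the point but does not remove it: Section 15 names a method whose standard form rests on an assumption that Section 13 breaks for named end points. The point is about a stated method, not a missing detail.

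**Conclusion.** The point holds for RR and Ti/Ttot, and for VTe if expressed per kg, at T1-T3. The equal-variance error term is invalid by design, and the PSV-SB P values from it cannot be relied on. What is certain is that the standard error is wrong, not which way. The 18% shortfall and 11% false positives (9% with CMV SD half the others) need single-time pooling, equal PSV and SB variances and the two-mean critical value. Pooling five times gives roughly 17% down to 3% for an awake SD of 0.5 to 1.5 times the SB SD. All SDs are assumptions.

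A reader might also take this as a flaw in the displayed data or the main result. It is neither: the mean ± SD summaries are computed within each group, and the primary comparison of LMA removal time, PSV against CMV, is a two-mean comparison outside this analysis. Severity: minor.

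**What to change.** For RR, Ti/Ttot and VTe per kg, state that PSV is compared with SB by separate-variance (Welch) contrasts using only those two groups, either at each of T1-T3 or on each patient's mean over T1-T3. As a precaution, apply a Greenhouse-Geisser correction to any within-patient F test kept over T0-T4.

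The change is to analysis wording only. Error degrees of freedom fall from 33 to 22 or fewer, so critical t rises from 2.03 to about 2.07 or slightly more. The extreme, if nearly all the variance lies in SB, is 12 − 1 = 11 degrees of freedom and a critical t of 2.20.
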